### Study Co-interventions

It will not be feasible to protocolize ventilator and general clinical management under pandemic conditions. Adjunctive non-antibiotic, non-interventional management of sepsis, acute respiratory distress syndrome, and glycemic control will be at the discretion of the patient's primary clinicians. Key aspects of clinical management (such as choice of antiviral, dose of administration, duration of treatment, ventilator strategy, treatment with inhaled nitric oxide, HFO, prone positioning, ECMO, additional antiviral/anti-inflammatory treatments and treated episodes of infection) will be documented either as part of the Influenza A H1N1 (Swine Flu) ICU (Registry) Study for participating centres or on separate data forms for centres not participating in the registry. Antibiotic therapy may be prescribed for suspected or confirmed concomitant bacterial infection at the discretion of the attending physician.

### H1N1 Testing

Local testing procedures may be used to facilitate diagnosis of H1N1. Where no local testing procedures exist, we recommend using the following initial and repeat testing procedures. For all new admissions to adult ICUs meeting study inclusion criteria and having no exclusion criteria with non-confirmed H1N1 (i.e., all suspected or probable cases) or where uncertainty exists regarding prior testing, we request the following sequence of laboratory tests:

#### Initial Diagnostic Testing (assuming diagnosis not confirmed at ICU admission)

1. Paired deep nasopharyngeal (NP) swab AND either an endotracheal (ET) aspirate or bronchoalveolar (BAL) (or sputum if not intubated) for (a) influenza polymerase chain reaction (PCR) and (b) viral culture; and

2. Endotracheal aspirate (or sputum if not intubated) for gram stain, culture and sensitivity (C & S)

#### Repeat Testing (for patients with one positive test)

1. Repeat both tests (PCR and viral culture) from the site that was *positive *previously (i.e., ET or BAL or NP swab). If both ET and NP swab were *positive*, send repeat ET aspirate specimen at day 7 and at weekly intervals thereafter.

2. After the first negative specimen(s) from a previously positive site, send a repeat specimen from the same site at 48 hours after the first specimen was collected.

### Drug Level Specimen Collection

To verify adequate absorption of rosuvastatin, we will draw venous blood for peak and trough plasma rosuvastatin concentrations (total of 2 specimens) on day 7 (+/- 1 day). Day 7 will be the preferred day for trough and peak specimen collection. A trough level specimen will be drawn prior to day 7 (+/- 1 day) dose. A peak concentration specimen will be drawn 3 to 5 hours after the dose of study drug is administered. A maximum of 80 patients will have blood drawn for drug concentration analysis; however, only patients randomized to rosuvastatin will have their samples analyzed. Samples will be labeled and batched at the site, for shipment to St Michael's Hospital (Toronto, Canada) for analysis after the study is unblinded.

### Follow-Up

Research staff will assess participants daily for adverse effects for the duration of treatment. CHAT study participants will have daily CK and liver function [aspartate aminotransferase (AST) and ALT] levels collected as part of the study protocol. Study drug will be discontinued if hypersensitivity is suspected (see Criterion 7 Completion of Study Drug Administration).

We will record the number of patients receiving full treatment and reasons for the inability to complete the assigned treatment duration (i.e., death, transfer to an alternate care facility, study withdrawal, etc). The study Data Safety and Monitoring Board (DSMB) will review all patients withdrawn from the study, safety data, and deaths.

All patients will be followed until death or hospital discharge. We will record the vital status of all patients at 90 days and hospital discharge, whichever occurs first. At day 60 patients remaining on the ventilator will be deemed ventilator dependent. Randomized patients will be considered successfully extubated when they remain off positive pressure ventilation (invasive or non-invasive ventilation) for 48 consecutive hours. If patients are re-intubated *within *48 hrs following extubation, they will be followed until they achieve one of the aforementioned outcomes. Patients discharged from the ICU and requiring readmission and re-initiation of mechanical ventilation (invasive or non-invasive) will be treated according to usual practice and will not be randomized on a second occasion to this study.

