### Completion of Study Drug Administration

Study drug administration will be stopped when one of the following conditions is met, whichever comes first:

1. 14 days after randomization

2. Hospital discharge (including transfer to an alternate care facility)

3. Death

4. CK noted to exceed 5,000 U/L (in the absence of an alternative diagnosis) or patient is determined to have clinical myositis or myopathy (at the discretion of the primary care team, patient may be re-challenged with study drug if CK or clinical findings no longer meet this criterion).

5. Alanine aminotransferase (ALT) exceeds 8 times the ULN (in the absence of an alternative diagnosis)

6. Co-administration of any of the following: niacin, fenofibrate, cyclosporine, gemfibrozil, lopinavir, ritonavir, oral contraceptives or estrogen

7. Attending physician or intensivist or SDM request to stop treatment.

We will request for data collection to continue in patients withdrawn from therapy prematurely. Clinicians will be encouraged to continue study medication despite negative H1N1 testing due to the potential for false negative results and the potential role for an anti-inflammatory agent (rosuvastatin) in severe lung disease. Decisions regarding continuation or discontinuation of antiviral treatment will be left to the discretion of the attending physician or intensivist.

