#### Secondary Outcomes

[2] Adherence to the medication administration regimen as outlined in the study protocol.

[3] Proportion of completed primary and secondary endpoints for the planned full CHAT trial that are collected.

[4] Number of patients who receive open-label statins.

[5] Number of consent withdrawals.

[6] Recruitment rates by approved consent model.

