### Data Collection

We will collect CHAT specific data starting at ICU admission using paper-based versions of the electronic data collection forms developed for the Influenza A H1N1 (Swine Flu) ICU (Registry) Study [7]. The forms will document baseline characteristics, enrolment into concurrent influenza research studies, co-morbidities, illness severity (**see **Additional File 4), vaccination status, co-interventions, feasibility outcomes and clinical outcomes for the planned definitive trial (primary: the proportion of patients successfully weaned from mechanical ventilation in less than 10 days; secondary: impact of rosuvastatin on ICU, 60 and 90 day, and hospital mortality and on ICU free days at day 60). In addition to the data forms developed for the Influenza A H1N1 (Swine Flu) ICU study, we developed 13 additional forms including an (i) eligibility and randomization form, (ii) severity of illness form, (iii) consent form, (iv) drug administration form, (v) H1N1 diagnostic test results form, (vi) laboratory data form, (vii) drug level (serum) specimen collection form, (viii) 60 day and 90 day outcomes form, (ix) comments and end of study investigator sign off, (x) protocol violation form: biochemistry, (xi) protocol violation form: medication administration/discontinuation, (xii) adverse event form, (xiii) serious adverse event form in randomized patients. For centres not participating in the registry, we drafted 10 additional forms to capture necessary demographic, treatment and outcomes information. In addition, we drafted a form to capture demographic data and outcomes on eligible but not randomized patients.

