### Statistical Analysis

Descriptive statistics will be used to summarize the data. For univariate analyses, we will use the Chi-square test (alternatively, Fisher's exact test when the expected cell size is ≤ 5) and Student's t-test (alternatively, the Mann-Whitney U-test, if normality assumptions are not satisfied) for binary and continuous outcomes, respectively. All analyses will be conducted on an intention-to-treat basis.

Feasibility for the pilot study will be assessed by metrics that reflect our capacity to ultimately recruit a representative sample of 1,050 patients in the planned full CHAT trial. We will consider the study to be feasible if we recruit at least 30% (commonly used threshold in ICU studies) of all eligible patients in participating ICUs through careful review of site screening logs. Additionally, we expect that: (i) less than 10% of medication doses will fail to be administered in the absence of meeting one of the medication discontinuation criteria; (ii) less than 5% of data forms will be missing important primary and secondary outcomes data required for the planned full CHAT trial and (iii) no more than 10% of enrolled patients will be withdrawn prematurely due to open label use of statins or withdrawal of consent. We will describe recruitment rates based on approved consent models. Since centres in Australia and New Zealand will be permitted to use Atorvastatin and matching placebo (instead of Rosuvastatin/matching placebo), we propose to conduct the planned primary and secondary analyses (i) using the pooled data (rosuvastatin plus atorvastatin) and (ii) using rosuvastatin (as the predominantly used statin in the CHAT Trial) data alone.

A DSMB will oversee the trial and will consist of 3 individuals with expertise in viral infectious diseases, statistics and clinical critical care of which one will be international. The DSMB will hold a teleconference after either 30 patients have evaluable data or approximately 8 months after study initiation. Should the trial be completed, feasibility data from the pilot study will be analyzed by the DSMB at the end of the study. This information will be conveyed to the Steering Committee. Together the DSMB and Steering Committee will formulate a decision whether to proceed with the full trial. Clinical outcomes will remain blinded by study group assignment with a view to including them in the planned larger trial.

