Several time-honored aspects of RCT design including the use of central randomization, preservation of allocation concealment, multi-level study blinding, and use of a matching placebo posed challenges to us in designing a pandemic protocol. We contemplated the necessity of including each of these study design features. After careful deliberation, we decided to include central randomization (using lists distributed by the study methods centre to participating centres), preserve multi-level blinding (by involving pharmacies at participating centres) and contract a local pharmaceutical company to prepare crushed drug and matching placebo (in the absence of industry supply of study drug and an available placebo). Recognizing that trial initiation may be delayed and recruitment curtailed if a priori in-person SDM consent was required, we considered use of alternative consent models. A priori in-person SDM consent not only hinges on the existence and availability of SDMs [39], but also the ability of SDMs to access hospitals during a pandemic.

Strengths of the proposed pilot trial design include the use of central randomization, allocation concealment, multi level blinding, standard criteria for medication discontinuation, and 90 day follow up. To ensure feasibility during a pandemic, we did not protocolize H1N1 testing, ventilator and sedation management or the clinical use of antibacterial agents. By merging study data with an Influenza Registry and capturing data on unique forms for centres not participating in the registry, we will, however, document key aspects of clinical management.

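### The Follow-Up rule records vital status at the earlier of day 90 and hospital discharge, contradicting the 60- and 90-day mortality endpoints and the claimed 90-day follow-up

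*Protocol article*

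**What the plan says.** Two consecutive sentences in the Follow-Up section set the rule. The first gives the duration: "All patients will be followed until death or hospital discharge". The second gives the time of ascertainment: "We will record the vital status of all patients at 90 days and hospital discharge, whichever occurs first".

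Three other places assume something different.

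- Data Collection lists the clinical outcomes of the planned definitive trial, which the pilot is to collect. After the primary endpoint (weaning from ventilation in under 10 days) come "secondary: impact of rosuvastatin on ICU, 60 and 90 day, and hospital mortality and on ICU free days at day 60". The same section names among the additional forms "viii) 60 day and 90 day outcomes form".
- The Discussion includes among the design's strengths "standard criteria for medication discontinuation, and 90 day follow up".
- Collecting these endpoints is itself an outcome of the pilot. Secondary outcome [3] is "Proportion of completed primary and secondary endpoints for the planned full CHAT trial that are collected", and Statistical Analysis expects that "less than 5% of data forms will be missing important primary and secondary outcomes data required for the planned full CHAT trial".

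**The concern.** Fixed-time mortality needs a status for every patient at that time, wherever the patient is. The Follow-Up rule stops at discharge, and its two sentences point the same way, so a site reading that section alone would have no instruction to look for a discharged survivor at day 60 or day 90. A site working from the outcomes form would look. The article thus gives two incompatible instructions.

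The issue is not a procedural detail left to a fuller document. It is a stated rule that, if followed, defeats endpoints listed elsewhere in the same article.

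One of the pilot's own questions is at stake: can the full trial's endpoints be collected under pandemic conditions? Follow-up after discharge is likely to be the hardest part of collecting 60- and 90-day mortality, and the literal rule leaves it out. Timing also matters. Statistical Analysis keeps clinical outcomes blinded by group so that they may enter the larger trial, and Other Considerations allows combining the data only if no important protocol modification follows the pilot. Correcting the ascertainment rule after the pilot could put that at risk, or leave pilot patients with a differently measured endpoint.

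**Working it through.** The article states no figure for this point that could be reproduced. The check compares the passages and then illustrates the size.

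**What the literal rule yields for each type of patient**

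| Course | Day-60 status | Day-90 status |
|---|---|---|
| Dies in hospital by day 90 | known | known |
| Discharged alive before day 60 | not recorded | not recorded |
| Discharged alive between days 60 and 90 | known (alive) | not recorded |
| Still in hospital at day 90 | known | known |

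The loss at day 90 therefore affects everyone discharged alive before day 90. The loss at day 60 affects only those discharged alive before day 60.

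**Inputs**

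- N = 80 (Sample Size Estimation).
- Hospital mortality m = 10% to 30% (Abstract, for the severe syndrome; used as illustration).
- Share of hospital survivors discharged before day 90, f: not in the article. Assumed range 50% to 100%.

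**Formula:** patients without day-90 status = N × (1 − m) × f.

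| m | f = 50% | f = 100% |
|---|---|---|
| 10% | 80 × 0.90 × 0.50 = 36 (45%) | 80 × 0.90 × 1.00 = 72 (90%) |
| 30% | 80 × 0.70 × 0.50 = 28 (35%) | 80 × 0.70 × 1.00 = 56 (70%) |

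The range is 28 to 72 of 80. The same formula applies at day 60 with the share discharged before day 60. That share is also not given and cannot exceed f, so the day-60 loss is at most the day-90 loss.

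**Against the 5% criterion, counting one outcomes form per patient**

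- 3/80 = 3.75% meets a limit of under 5%; 4/80 = 5.0% does not.
- Four patients are 4/72 = 5.6% of survivors at m = 10%, or 4/56 = 7.1% at m = 30%.

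The criterion thus fails once about 6–7% of survivors leave hospital before day 90, far below the assumed range. On this count the conclusion does not depend on where f lies between 50% and 100%.

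**If discharge status is accepted as day-90 status instead**, no form is missing and the criterion can be met. The quantity measured is then death in hospital by day 90, with every discharged patient counted as alive, and outcome [3] says nothing about ascertainment after discharge.

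**After the correction**, no day-60 or day-90 status is missing by design. Only true loss to follow-up remains, and the criterion allows at most 3 of 80 patients.

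**The case against.** The best defence is that this is a drafting slip. The Follow-Up sentence is awkward in itself: it joins two time points and then selects one. The named 60/90-day form, the separate listing of 60- and 90-day mortality, and the Discussion's claim all suggest that fixed-time follow-up was intended. That stands, and it is why the point is an internal contradiction rather than a deliberate design choice. It does not remove the need for correction, because the sentence on follow-up until death or discharge supports the restrictive reading.

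A second defence is scale. This is a feasibility pilot whose primary outcome is the proportion of eligible patients enrolled, and the full trial's primary endpoint does not use day-90 status. That also stands and limits the severity.

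A third is the denominator. The 5% criterion speaks of data forms, and the article does not say which. Over all 13 additional forms for each patient (80 × 13 = 1,040), 28 to 72 missing would be 2.7% to 6.9%, so failure would not be certain. The statement that the criterion fails by design rests on one outcomes form per patient.

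A reader might infer several stronger claims that the article does not support:

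- *That 60- and 90-day mortality cannot be obtained at all.* This is true only under the Follow-Up rule, and for day 60 only for discharges before day 60.
- *That the pilot would never attempt the collection.* The outcomes form exists for that purpose.
- *That the 60- and 90-day endpoints merge into one.* In-hospital deaths by day 60 and by day 90 remain different quantities.
- *That ICU readmissions are lost.* Those within the same hospital stay are still followed.
- *That patients transferred elsewhere also leave follow-up.* Transfer counts as discharge in the rule for completing study drug; the Follow-Up section does not adopt that meaning.

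**Conclusion.** The contradiction is real and of moderate severity. The Follow-Up section, as written, is incompatible with the endpoints and form in Data Collection and with the 90-day follow-up claimed in the Discussion.

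The estimate of 28 to 72 of 80 patients without day-90 status rests on three assumptions: sites follow the Follow-Up wording rather than the form, the Abstract's mortality range applies to the trial's patients, and half to all survivors leave hospital before day 90. The contradiction itself needs none of these.

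The consequence is confined to secondary outcome [3], the missing-data criterion that supports it, and the secondary mortality endpoints of the planned full trial. The pilot's primary outcome is unaffected.

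**What to change.** Replace the vital-status sentence in Follow-Up with: *Vital status will be recorded for all randomized patients at hospital discharge and at day 60 and day 90 after randomization, regardless of earlier discharge.* Amend the preceding sentence on follow-up until death or discharge so that it does not override this, and align Data Collection and the Discussion with the same rule.

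The cost is a telephone or record check for discharged survivors (at most about 72 of 80 at 10% hospital mortality), with permission for that contact covered in the REB submission. The permission deserves attention because the article prefers a waiver of consent. The 60/90-day outcomes form already exists, so no new form is needed.

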### Sample Size Estimation (CHAT Pilot Trial)

Estimates are not available to allow precise sample size estimation of the primary outcome for the proposed CHAT pilot RCT. We propose to undertake a pilot study in a convenience sample of 80 patients with suspected, probable or confirmed H1N1 infection to assess trial feasibility.

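### The follow-up rule as written stops vital-status recording at hospital discharge, which contradicts the 60- and 90-day mortality endpoints and the claimed 90-day follow-up

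*Protocol article*

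**What the plan says.** The Follow-Up section of the protocol article sets the horizon in two consecutive sentences. The first is general: "All patients will be followed until death or hospital discharge". The second concerns survival: "We will record the vital status of all patients at 90 days and hospital discharge, whichever occurs first".

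Three other places assume a longer horizon:

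- Data Collection lists the clinical outcomes that the pilot forms will document for the planned definitive trial, among them "secondary: impact of rosuvastatin on ICU, 60 and 90 day, and hospital mortality and on ICU free days at day 60".
- The same section lists the study's own forms, including "viii) 60 day and 90 day outcomes form".
- The Discussion counts among the design's strengths "standard criteria for medication discontinuation, and 90 day follow up".

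The pilot also tests whether these endpoints can be collected. Secondary outcome [3] is "Proportion of completed primary and secondary endpoints for the planned full CHAT trial that are collected", and Statistical Analysis sets the expectation that "less than 5% of data forms will be missing important primary and secondary outcomes data required for the planned full CHAT trial".

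**The concern.** A fixed-time mortality endpoint needs the patient's status at that time, wherever the patient is. The Follow-Up rule ties the last recording of status to discharge whenever discharge comes before day 90. A site that follows the rule exactly has nothing to enter at day 60 or day 90 for a patient who went home on day 20.

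This matters in a pilot because collecting the endpoints is itself under test. There are two ways to score such a patient, and neither helps:

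- If day-60 and day-90 status count as missing, the pilot can fail its missing-data criterion although every site complied.
- If status at discharge counts as complete, the criterion can be met without any test of tracing patients after discharge, which the full trial would need for 60- and 90-day mortality.

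Other Considerations also allows pilot data to be combined with the larger trial under stated conditions. If that happened, the gap would pass into the larger trial's mortality data, and an analysis plan cannot restore status that was never recorded.

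**Working it through.** The article gives no figure to reproduce here: the pilot size is a "convenience sample of 80 patients with suspected, probable or confirmed H1N1 infection", without a power calculation. The check is a comparison of text, followed by an illustration of scale.

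**Step 1. Apply the Follow-Up rule to each type of patient.**

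| Patient | Earlier event | Day-60 status | Day-90 status |
|---|---|---|---|
| Dies in hospital by day 60 | death | known | known |
| Dies in hospital after day 60, by day 90 | death | known (alive) | known |
| Discharged alive before day 60 | discharge | not recorded | not recorded |
| Discharged alive between days 60 and 90 | discharge | known (still in hospital) | not recorded |
| Still in hospital at day 90 | day 90 | known | known |

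Day-60 status is therefore lost only for live discharges before day 60, and day-90 status for all live discharges before day 90. The article describes no contact or record check after discharge that would fill these cells.

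**Step 2. Illustrate the scale.** Inputs from the article: N = 80 (Sample Size Estimation) and hospital mortality m of 10-30% in severe disease (Abstract, Background), applied here to the trial population. Assumption: f, the share of hospital survivors discharged before day 90, for which the article gives no figure.

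Number without day-90 status = N × (1 − m) × f

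- f = 1, m = 30%: 80 × 0.70 × 1 = 56 (70%)
- f = 1, m = 10%: 80 × 0.90 × 1 = 72 (90%)
- f = 0.5, m = 30%: 80 × 0.70 × 0.5 = 28 (35%)
- f = 0.5, m = 10%: 80 × 0.90 × 0.5 = 36 (45%)

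**Step 3. Compare with the plan's limit.** The criterion counts data forms. Taking one 60/90-day form per patient (an assumption), 5% is 0.05 × 80 = 4 forms. The share of survivors discharged before day 90 that already reaches this limit is 0.05 / (1 − m): 0.05 / 0.90 = 5.6% and 0.05 / 0.70 = 7.1%.

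**The case against.** The strongest reply is that this is a slip of wording and not a censoring rule. The sentence is awkward in itself: it joins two time points with a conjunction and then asks for the earlier of them. A dedicated 60/90-day form and the 90-day follow-up named in the Discussion show what the authors meant to do, and an article may leave tracing procedures to the full protocol. This stands as far as intent goes. A reader might infer that day-60 and day-90 status would never be obtained; the documents do not support that as a statement about practice. It does not rescue the rule, because the article does more than omit detail: it states an instruction that conflicts with its own endpoints.

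A second reply is that little hangs on it. The pilot's primary outcome is the proportion of eligible patients enrolled. The planned full trial's primary outcome is weaning from ventilation in less than 10 days. Neither uses day-60 or day-90 survival. Pooling is conditional, and changes to the larger protocol are expected after the pilot. All of this is correct and limits the point to secondary endpoints, outcome [3] and the missing-data criterion.

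Several stronger readings are tempting but not supported:

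- *Hospital mortality is cut off at day 90.* The preceding sentence follows patients to death or discharge with no cap, so at most the two sentences are in tension.
- *All the mortality endpoints collapse into one quantity.* ICU mortality is untouched, and in-hospital death by day 60 differs from in-hospital death by day 90.
- *90-day mortality is understated by a given number of percentage points.* The article gives no death rate after discharge. Such a figure would also treat discharged patients as alive, whereas the counts above treat them as missing.
- *One arm would look safer.* Nothing in the article shows that length of stay would differ by arm, and clinical outcomes stay blinded by group when feasibility is judged.
- *ICU-free days must also be redefined.* That is a separate question of definition, which an article may leave to the full protocol.

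**Conclusion.** The point holds as an internal contradiction. The Follow-Up rule, applied as written, cannot deliver the 60- and 90-day mortality listed under Data Collection or the 90-day follow-up claimed in the Discussion. That conclusion rests on the text alone.

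The size is illustrative. It depends on background mortality being applicable to the enrolled patients and on the share of survivors discharged before day 90, which is assumed. Under either share shown, the count without day-90 status is far above 4 of 80, given one form per patient. The comparison with the 5% limit would change if the criterion were counted over all forms.

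**What to change.** Replace the vital-status sentence in Follow-Up with: *Vital status will be recorded for every randomized patient at day 60 and day 90, whether or not still in hospital, and separately at hospital discharge.* The general sentence before it should be made subject to this, so that the two agree with each other and with Data Collection and the Discussion.

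The cost is a brief contact or record check for patients who have left hospital, entered on the existing 60/90-day form. It is best done before follow-up proceeds, since status not collected during the pilot may be hard to recover later. If the full protocol already requires status at both days regardless of discharge, only the article's sentence needs correcting.
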